# Rationale and design of the THIRST Alert feasibility study: a pragmatic, single-centre, parallel-group randomised controlled trial of an interruptive alert for oral fluid restriction in patients treated with intravenous furosemide

**DOI:** 10.1136/bmjopen-2023-080410

**Published:** 2024-01-12

**Keywords:** Heart failure, Randomized Controlled Trial, Feasibility Studies, Electronic Health Records

## Abstract

**Introduction:**

Acute heart failure (HF) is a major cause of unplanned hospitalisation characterised by excess body water. A restriction in oral fluid intake is commonly imposed on patients as an adjunct to pharmacological therapy with loop diuretics, but there is a lack of evidence from traditional randomised controlled trials (RCTs) to support the safety and effectiveness of this intervention in the acute setting.

This study aims to explore the feasibility of using computer alerts within the electronic health record (EHR) system to invite clinical care teams to enrol patients into a pragmatic RCT at the time of clinical decision-making. It will additionally assess the effectiveness of using an alert to help address the clinical research question of whether oral fluid restriction is a safe and effective adjunct to pharmacological therapy for patients admitted with fluid overload.

**Methods and analysis:**

THIRST (Randomised Controlled **T**rial within the electronic **H**ealth record of an **I**nterruptive alert displaying a fluid **R**estriction **S**uggestion in patients with the treatable **T**rait of congestion) Alert is a single-centre, parallel-group, open-label pragmatic RCT embedded in the EHR system that will be conducted as a feasibility study at an National Health Service (NHS) hospital in London. The clinical care team will be invited to enrol suitable patients in the study using a point-of-care alert with a target sample size of 50 patients. Enrolled patients will then be randomised to either restricted or unrestricted oral fluid intake. Two primary outcomes will be explored (1) the proportion of eligible patients enrolled in the study and (2) the mean difference in oral fluid intake between randomised groups. A series of secondary outcomes are specified to evaluate the effectiveness of the alert, adherence to the randomised treatment allocation and the quality of data generated from routine care, relevant to the outcomes of interest.

**Ethics and dissemination:**

This study was approved by Riverside Research Ethics Committee (Ref: 22/LO/0889) and will be published on completion.

**Trial registration number:**

NCT05869656.

STRENGTHS AND LIMITATIONS OF THIS STUDYTHIRST Alert is a pragmatic randomised controlled trial where all elements of trial conduct are embedded within the routine care clinical pathway.The intervention and programme theory has been codesigned with a multidisciplinary team including physicians, nurses, clinical informatics officers and patient representatives.A proportionate consent model has been approved for use to help with the practicality of trial conduct.Uncertainty remains regarding data quality in relation to the ascertainment of study outcomes from routine hospital care records.

## Introduction

Acute heart failure (HF) is an important cause of unplanned hospitalisation and is characterised by excess body water, also known as congestion.^1 2^ Despite being a common clinical problem, there is a lack of high-quality evidence to guide drug treatment and non-pharmacological measures.^3^ Restriction of oral fluid intake is commonly used as an adjunct to pharmacological therapy but its effectiveness is uncertain and may exacerbate symptoms of thirst, as suggested by the limited randomised controlled trials (RCTs), which have been conducted to date.^4–6^ These previous trials achieved only small differences in oral fluid intake, which may reflect the Hawthorne effect whereby participation in a clinical trial influences fluid intake in both groups.^7^

Patients and clinicians identify the need for better treatment of fluid overload as a key priority, and the use of oral fluid restriction also highlighted a gap in evidence in clinical practice guidelines.^2^
^8^
^9^ To address this evidence gap and some of the challenges encountered in previous studies, we designed a pragmatic RCT embedded in the electronic health record (EHR) system to evaluate the safety and effectiveness of oral fluid restriction in acute HF.

### Patient population

Fluid overload may be caused by liver or kidney dysfunction,^10 11^ as well as by HF, with similar evidence gaps for congestion management in such circumstances.^12–14^ However, a reliance on evaluating interventions for the immediate management of fluid overload only where the underlying cause is established may impact the generalisability of any findings. Given that standardised clinical scores for congestion are not well validated or adopted in practice,^15 16^ we used the prescription of two consecutive doses of intravenous furosemide within the first 48 hours of admission as evidence of a physician-assessed ‘treatable trait’ of fluid congestion, to define the study population.^17^

At our proposed study site, more than one consecutive dose of intravenous furosemide was administered during the first 48 hours of admission in 1537 unplanned admissions between April 2019 and October 2022. In 56% of these admissions with available supporting data, oral fluid restriction was recommended (online supplemental appendix 1). The use of prescribing intention to identify the study population enabled digital enrolment into the study based on a discrete triggering event. To our knowledge, there has been no previous RCT conducted in all patients treated for congestion with intravenous furosemide in the acute care setting.

10.1136/bmjopen-2023-080410.supp1Supplementary data

### Pragmatic research

There are many evidence gaps in routine clinical practice that have not been addressed by conventional RCTs, which may be prohibitively expensive. Pragmatic clinical trials (PCTs) offer a potential solution, particularly relevant to the evaluation of low-risk interventions where clinical equipoise may exist. By integrating a randomisation procedure into routine care pathways, automating case identification through the EHR, engaging the clinical care team for patient recruitment and using routinely collected data for trial outcomes, there is the potential to perform large-scale trials at low-cost and low burden to patients and their caregivers. Many questions remain, however, about how best to deliver PCTs embedded in EHR systems, including the design of physician-facing alerts and different models of consent. For our study, we employ an interruptive alert to provide the routine care team with an invitation to enrol eligible patients, and use a proportionate process for consent that can be delivered by the same team.

PCTs have the potential to enable evidence generation during routine care, helping to conduct more efficient and representative trials.^18^ Through examining the comparative effectiveness of existing interventions that have demonstrable variation in practice, many evidence gaps may be addressed. The use of oral fluid restriction in patients who are treated pharmacologically for fluid overload in the setting of acute unplanned care represents one such gap.

The THIRST (Randomised Controlled **T**rial within the electronic **H**ealth record of an **I**nterruptive alert displaying a fluid **R**estriction **S**uggestion in patients with the treatable **T**rait of congestion) Alert trial, therefore aims to examine (1) whether interruptive alerts are an effective means to engage the usual care team to enrol patients into a pragmatic RCT and (2) for enrolled patients, whether the randomised assignment to either oral fluid restriction to 1 L per day or no oral fluid restriction leads to a difference in documented oral fluid intake. The evidence generated will be used to inform the design of subsequent multicentre outcomes-driven PCTs embedded in EHR systems.

## Methods and analysis

### Study design

THIRST Alert is a single-centre, parallel-group, open-label pragmatic RCT embedded in the EHR system that will be conducted as a feasibility study.^19^ The study will be delivered entirely at University College Hospital, UCLH, a digitally mature National Health Service (NHS) hospital.^20^ Enrolment started in May 2023 and the estimated trial completion date is December 2023. Given the low-risk nature of the intervention, a verbal, opt-out consent model is used. The study protocol has been prepared with reference to the Standard Protocol Items: Recommendations for Interventional Trials (SPIRIT) statement.^21^ The trial is registered at ClinicalTrials.gov (NCT05869656).

### Study procedures

An overview of the study procedures is given in figure 1. The trial was designed to be integrated into the EHR system EPIC (Epic, Epic Systems, Verona, Wisconsin, USA). The screening and identification of eligible patients, display of interruptive alerts to physicians, randomisation and outcome ascertainment are all provisioned within EPIC.^22^ Education events, internal communication and email correspondence were delivered to members of the routine care team to raise awareness of the study but no formal cointerventions were undertaken. The conduct and analysis of the trial are overseen by a trial management group that conceived a programme theory for the alert with relevant multidisciplinary input (online supplemental appendix 2,3). The enrolment invitation and randomised treatment recommendations are classified as complex interventions according to the Medical Research Council framework.^23^

**Figure 1 F1:**
[figure not shown]
THIRST Alert trial patient flow. RCT, randomised controlled trial; THIRST, Randomised Controlled Trial within the electronic Health record of an Interruptive alert displaying a fluid Restriction Suggestion in patients with the treatable Trait of congestion; UCLH, University College London Hospital.

The trial is designed to maximise the generalisability and applicability of the evidence generated and is highly pragmatic according to the PRagmatic Explanatory Continuum Indicator Summary-2 (PRECIS-2) framework (figure 2).^24^

**Figure 2 F2:**
[figure not shown]
PRECIS-2 score for the THIRST Alert trial. Each of the nine domains are scored on a 5-point Likert continuum (from 1=very explanatory ‘ideal conditions’ to 5=very pragmatic ‘usual care conditions’). PRECIS-2 score, The PRagmatic Explanatory Continuum Indicator Summary-2 score; THIRST, Randomised Controlled Trial within the electronic Health record of an Interruptive alert displaying a fluid Restriction Suggestion in patients with the treatable Trait of congestion.

### Study participants

Adults of 18 years or older who were administered more than one dose of intravenous furosemide within the first 48 hours of an unplanned admission were eligible for the study. Patients admitted to a surgical, maternity or critical care ward were excluded (table 1).

**Table 1 T1:** Eligibility criteria for thirst alert study participants

Study participants	Eligibility criteria
Patients	**Inclusion** Aged 18 years and over Prescribed intravenous furosemide during the first 48 hours of their admission as a regular prescription rather than a one-off dose. Assessed as being suitable for inclusion in the trial by the responsible clinical team, that is, fluid restriction deemed to be in equipoise. **Exclusion** Surgical or obstetric wards Critical care wards
Prescribing clinicians: physicians (consultants and junior doctors)	Any clinician with prescribing rights and who prescribes more than one dose of intravenous furosemide within 48 hours of admission, during the trial recruitment period.
Nursing staff	A separate order is triggered for enrolled patients and only presented to nursing staff who access their patient record to help facilitate fluid balance documentation.

### The interruptive alert inviting usual care team to enrol eligible patients

Any member of the clinical team may receive an interruptive alert (online supplemental appendix 4 figure 1A) during their interaction with EPIC for an eligible patient, informing them of the study and inviting them to enrol the patient. The clinician can click the appropriate button on the alert to enrol, decline to enrol or defer the decision regarding enrolment. The alert is non-coercive, and the decision about patient enrolment is at the discretion of the treating clinician. We anticipate that physicians will enrol patients in cases where they judge that there is clinical equipoise as to whether oral fluid restriction is likely to benefit the patient. The alert was designed and tested with EPIC application specialists in an iterative manner, integrating feedback from end-users on the wording of the design.

### The randomised treatment intervention

After enrolment of patients in the study, the routine care team receives a recommendation regarding oral fluid intake and assignment is determined by point of care randomisation. The randomised treatment allocation is only presented to the clinical team after they click ‘yes’ to the THIRST alert, rather than displayed immediately, to minimise the possibility of differential recruitment to the treatment arms of the trial. For patients allocated to the intervention group, the routine care team received a recommendation for a target oral fluid restriction of 1 L per day; for patients allocated to the control group, the care team received a recommendation for unrestricted oral fluid intake (online supplemental appendix 4 figure 1B,C). The oral fluid restriction target was chosen based on previous RCTs and acceptability in clinical practice.^4–6^ The randomised treatment recommendation for both groups additionally advises the clinician to: (1) complete an EPIC order for fluid balance monitoring; (2) document the treatment allocation in the clinical notes; (3) inform the patient and the nursing team and (4) provide the patient with a participant information sheet (PIS).

### Randomisation and blinding

Subjects will be randomised 1:1 using an internal random number rule implemented using a standard EPIC randomisation tool used in other PCTs.^25^ No block randomisation or additional covariate balancing will be undertaken. The study is open label with patients and their care teams being made aware of the treatment allocation.

### Study outcomes

#### Primary outcomes

Number of eligible patients randomised.Difference in oral fluid intake between intervention and control arms.

#### Secondary outcomes

Adherence to randomised treatment recommendation.Proportion of alerts resulting in clinical orders for nursing care.Oral fluid intake.Net fluid balance.Weight change after randomisation.Length of stay.Frequency of blood test measurements of renal function.Prescription of diuretic medications.Daily change in creatinine.Patient-reported outcome measures.

These outcomes were chosen based on clinical relevance and the ability to detect the possibility of attributable harm during an inpatient admission.

### Sample size and power calculation

No formal sample size calculation was performed given the primary outcomes pertain to the feasibility of using an EHR alert aimed at the routine care team to (1) enrol eligible patients into an RCT of oral fluid restriction and (2) cause and sustain the allocated clinical treatment effect, as measured by documented oral fluid intake. This is in keeping with the role of feasibility studies used by other groups.^26^ Our target sample size was 50 patients, based on the predicted number of eligible patients at the study site during the recruitment period.

### Data collection, curation and storage

Baseline characteristics and study outcomes will be extracted from the routine care record. Information on the frequency of the interruptive alert and staff responses to alerts will be recorded in EPIC. We will also extract primary and secondary International Classification of Diseases (ICD)-10 diagnosis codes assigned to the clinical episode by the clinical coding team. Study data will be transferred to a secure research environment within UCLH NHS Foundation Trust as pseudoanonymised electronic case report forms (eCRFs). No data will leave the UCLH NHS system. Patients who opt out or withdraw from the trial will have their decision documented on the eCRF and their data will not be included in the main analysis.

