### Ethics and dissemination

This study protocol was approved by the London Riverside Research Ethics Committee (Ref: 22/LO/0889) and sponsored by University College London (Ref: 151938). A verbal opt-out model of consent was adopted based on the negligible risk associated with the intervention. Patients are informed of their study participation and of their treatment allocation and can opt-out of the study or decline to follow the recommendation for oral fluid restriction at any time. A copy of the sample PIS is provided to patients (online supplemental appendix 5). The data management for the trial conforms to NHS Information standards DCB0129 and DCB0160 and was approved by University College London Hospitals NHS Foundation Trust (UCLH) Digital Services Safety board.^30^ The alert is not classified as a separate piece of software but is incorporated within the Epic EHR, which is registered as a class I medical device by the UK Medicines and Healthcare products Regulatory Agency.^31 32^ The study findings will be disseminated through publication in open-access peer-reviewed journals and through the provision of reports for patients and clinicians involved in the study. As a feasibility study, the findings shared will include trial evaluation, and whether alerts which ‘nudge’ clinicians to recruit patients into pragmatic, low-risk comparative effectiveness trials,^33^ are a scalable way to conduct efficient RCTs.^18^ The THIRST Alert feasibility study will share insights that inform the design and execution of future integrated approaches to evidence generation from routine care.

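### Patients who opt out or withdraw after randomisation, with their arm disclosed, are left out of the main analysis, so the fluid-intake comparison may be biased by arm-dependent exclusion

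*Protocol article*

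**What the plan says.** The rule is in the Protocol article, Data collection, curation and storage. Patients who opt out or withdraw will have "their decision documented on the eCRF and their data will not be included in the main analysis". It makes no distinction by arm, by timing, or between leaving the trial and refusing use of routine data.

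Four other sections fix when such a decision can occur:

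- Study design: "a verbal, opt-out consent model is used".
- The randomised treatment intervention: "The randomised treatment allocation is only presented to the clinical team after they click" yes on the alert. The recommendation then displayed advises the clinician, among other steps, to "inform the patient and the nursing team" and to hand over the information sheet.
- Randomisation and blinding: "Subjects will be randomised 1:1 using an internal random number rule", and "The study is open label with patients and their care teams being made aware of the treatment allocation".
- Ethics and dissemination: "Patients are informed of their study participation and of their treatment allocation and can opt-out of the study or decline to follow the recommendation" at any time.

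The between-arm difference in oral fluid intake is a primary outcome. The Statistical analysis plan section gives 250 mL/day as the clinically relevant difference, makes progression depend partly on the primary outcome targets, and neither adjusts for nor imputes missing data.

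**The concern.** Randomisation makes the two arms comparable only if the patients analysed are those randomised, or if losses are unrelated to arm and outcome. Here a patient's decision to leave comes after allocation and with the arm disclosed. The Introduction says fluid restriction may exacerbate thirst, so it is plausible that leaving differs by arm and is related to how much a patient would drink. If so, the main analysis compares selected groups.

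The article withholds the allocation from the clinician until enrolment precisely to limit differential recruitment. Excluding later opt-outs lets a similar selection back in. The sample size section also describes the second primary aim as whether the allocated treatment effect can be produced and sustained. A patient who leaves because of the allocated arm is informative for that aim, yet contributes nothing to the main estimate.

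At stake is the fluid-intake difference that informs the stop/go decision and, to a lesser degree, the secondary comparisons made on the same patients.

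**Working it through.** **Sequence of events.** Reading the sections together: the clinician accepts the alert; the patient is randomised; the allocation is shown to the team; the team is advised to tell the patient and give the information sheet; the patient may then opt out. A patient's opt-out or withdrawal therefore follows randomisation, with the arm known or knowable.

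**No figure to reproduce.** The article reports no formal sample size calculation and gives no SD and no opt-out rate. What follows only illustrates size.

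**Inputs from the article.** Target 50 patients, 1:1, so about 25 per arm; clinically relevant difference 250 mL/day.

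**Assumptions.** Normally distributed mean daily intake with SD 500 mL; a fraction f of the restricted arm excluded and none of the control arm; correlation rho of 0.3 to 0.5 between intake and propensity to leave.

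**Formula.** Excluding the fraction f with the highest propensity to leave lowers the analysed restricted-arm mean, and so raises the control-minus-restricted difference, by

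shift = rho × SD × phi(z) / (1 − f), where z is the standard normal quantile at 1 − f.

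| Leavers of 25 | f | phi(z)/(1 − f) | Shift, rho 0.3 | Shift, rho 0.5 |
|---|---|---|---|---|
| 1 | 4% | 0.0862/0.96 = 0.0898 | 13.5 mL/day | 22.4 mL/day |
| 5 | 20% | 0.2800/0.80 = 0.3500 | 52.5 mL/day | 87.5 mL/day |

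Against 250 mL/day, that is about 5% to 9% at 4% loss and 21% to 35% at 20% loss. The shift is proportional to the SD: at 20% loss it is 31.5 to 52.5 mL/day for SD 300 and 73.5 to 122.5 mL/day for SD 700.

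**A second, simpler model.** If leavers would drink 1 SD more than those who stay, the shift is f × SD. For 3 of 25 leaving, 0.12 × 500 = 60 mL/day, or 24% of 250.

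**Chance of observing at least 250 mL/day when the true difference is 150.**

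- All 50 analysed: SE = 500 × √(2/25) = 141; (250 − 150)/141 = 0.71; chance 24%.
- One restricted patient excluded (25 v 24): SE = 500 × √(1/25 + 1/24) = 143; expected difference 163.5 to 172.4; chance 27% to 29%.
- Five excluded (25 v 20): SE = 500 × √(1/25 + 1/20) = 150; expected difference 202.5 to 237.5; chance 38% to 47%.

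**Loss in both arms.** The same formula applies to the control arm, and the two shifts subtract. With equal f and equal rho the net shift is zero. If loss were greater or more selective in the control arm, with high drinkers leaving, the difference would be understated instead.

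**The case against.** The strongest reply has four parts.

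1. The article separates opting out of the study from declining the recommendation, and the exclusion applies only to those who opt out or withdraw. A thirsty patient in the restricted arm can stop restricting and still be analysed. This stands. A reader might infer that non-adherers are dropped, or that the restricted arm is necessarily self-selected for tolerance; the article supports neither.

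2. Nothing shows that only the restricted arm loses patients. Both arms are recommended a fluid balance monitoring order, and restriction was recommended in 56% of comparable past admissions with data, so leaving the unrestricted arm is also plausible. This stands too. It is tempting to say that the unrestricted arm carries no burden and that the bias must favour the intervention, but the article gives no opt-out rates. At 4% loss the shift is far below the sampling SE of about 141 mL.

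3. Opt-outs are recorded on the eCRF, and the term main analysis leaves room for others. So the article does not support saying that opt-outs will go uncounted or that tolerability will be misreported. By-arm tables and sensitivity analyses may be in documents not shown, and their absence here is not the point. The point is the stated content of the main analysis.

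4. Under verbal opt-out consent, an initial opt-out may be the patient's first chance to refuse, and removing the data may be a condition of the approval. The information sheet is not shown. This limits the remedy. It does not justify a rule that treats every later withdrawal as a refusal of data use.

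**Conclusion.** The concern holds as a risk of bias built into a stated rule, not as a demonstrated bias. Followed as written, the main analysis departs from the randomised groups for a primary outcome that feeds the stop/go decision.

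The illustrated inflation runs from about 13.5 to 22.4 mL/day (one of 25 lost) to 52.5 to 87.5 mL/day (five of 25). It rests on an assumed SD of 500 mL, loss in the restricted arm only, and a correlation of 0.3 to 0.5. It is near zero under equal, equally selective loss and can reverse. The rise from 24% to 38–47% in the chance of reaching 250 mL/day belongs to the 20% versus 0% scenario alone.

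This is a feasibility study of 50 patients, and progression rests on several criteria, including data quality. The point should be fixed, but it is not grave enough to be a condition for the study.

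**What to change.** Replace the exclusion sentence with wording to this effect:

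*The main analysis includes all randomised patients in the arm to which they were allocated, including those who decline to follow the recommendation. For patients who opt out or withdraw, data up to that time are kept, and later routine-record data are kept where the ethics approval and participant information sheet permit. Only patients who refuse use of their data are removed; an initial opt-out counts as such a refusal if the consent model treats it so.*

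Report opt-outs, withdrawals and data refusals separately by arm, and keep the present exclusion as a sensitivity analysis.

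Cost: no extra patients and no new data collection, since outcomes come from the routine record. The consent terms must be checked, and an amendment may be needed. The article gives an enrolment start of May 2023 and estimated completion in December 2023, so some patients may already have opted out under the existing terms, and those terms govern their data. The estimated difference may also turn out smaller.
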